### Participant timeline {13}

Following randomisation, eligible participants visiting the study health facilities are being enrolled (Table 1). In the intervention arm, referral details are being registered and tracked through the DINKNESH referral and follow-up app. Feedback is being recorded upon the patient’s arrival at the referral facility, marking the end of the participant’s study period. In the control arm, referrals are following routine care procedures, and medical records are being reviewed 60 days after referral to assess diagnosis and feedback. The 60-day cutoff for each study participant is based on GBCI recommendations for timely diagnosis [5].

**Table 1 Tab1:**
[figure not shown]
Study timeline for e-health–supported referral of breast abnormalities at primary healthcare facilities in Ethiopia: cluster randomised controlled trial protocol

X: tasks will be completed

### Sample size {14}

The sample size was calculated following established methods for cluster randomised trials [21]. The calculation aimed to detect an increase in the proportion of complete referrals from 52% (based on a study in Tanzania [22]) to 70% in the intervention group. Using 80% power and a 5% significance level, and assuming an intra-cluster correlation coefficient of 0.01, the sample size was adjusted for clustering. With 8 clusters (4 intervention and 4 control) and equal allocation, the required sample size under individual randomisation was 222. After adjusting for the design effect due to clustering, the total required sample size increased to 282, corresponding to approximately 35 individuals per cluster.

### Recruitment {15}

All women with self-reported or CBE-detected breast abnormalities are being invited by trained staff at the health facilities to voluntarily participate in the study. Enrolment will continue until the required sample size of 35 participants is reached at each clustered facility. Once the target number is achieved, no additional participants will be included.

## Assignment of interventions: allocation

### Sequence generation {16a}

To ensure balance between the intervention and control groups, randomisation was stratified by health facility type. Among the eight clusters, two cluster health facilities are primary hospitals; therefore, these two primary hospitals were randomised first. The remaining six health centres were then randomly allocated to the intervention and control groups. The random allocation was conducted by an independent statistician using the lottery method.

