## Statistical methods

### Statistical methods for primary and secondary outcomes {20a}

#### Primary outcome (proportion of complete referrals)

All outcome measures will be analysed using IBM SPSS Statistics 25.0. Baseline differences between the intervention and control groups will be assessed using the independent samples *t*-test for continuous variables and the chi-square (χ^2^) test for categorical variables. To assess the effect of the intervention on the proportion of successfully completed referrals, a mixed-effects logistic regression model will be used, adjusting for potential confounders and accounting for clustering at the health facility level. Results will be reported in accordance with the CONSORT guidelines for reporting clinical trials.

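### Allocation was stratified by facility type, but the outcome models do not name facility type as a covariate; if completion differs by type, precision is given up

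*Protocol article*

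**What the plan says.** Under Sequence generation {16a} the protocol says that "randomisation was stratified by health facility type". It explains that "two cluster health facilities are primary hospitals; therefore, these two primary hospitals were randomised first", and that "The remaining six health centres were then randomly allocated to the intervention and control groups". The Sample size section {14} has four clusters per arm. Stratification with a four-to-four split implies one hospital and three health centres in each arm; this is inferred, not stated.

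Under Statistical methods {20a}, for the primary outcome, "a mixed-effects logistic regression model will be used, adjusting for potential confounders and accounting for clustering at the health facility level". The secondary outcomes (timely diagnosis, internal referrals, early-stage cancers) get models with the same kind of wording, and the Abstract repeats it for the trial as a whole. Facility type is named in none of these places. It is not excluded either, because the confounders are not listed.

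**The concern.** Stratifying takes facility-type variation out of the comparison of arms. The analysis benefits only if the model also takes that variation out of the error term. A random intercept for facility does not do this: it treats a systematic gap between hospitals and health centres as random between-cluster variation and charges it to the standard error of the arm effect, although the gap cancels in the arm contrast.

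The criterion the protocol does give for choosing covariates works against the stratification factor. A confounder must be associated with arm. At 35 women per facility, each arm would have 35 hospital women and 3 × 35 = 105 health-centre women, so facility type is unrelated to arm. Any reading of confounder that depends on imbalance would pass over the one factor the design controlled.

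At stake is precision in a trial with only eight clusters, where avoidable between-cluster variance is expensive. The trial is also unblinded and already enrolling, so an unnamed covariate leaves a choice that could be made after outcome data have been seen.

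**Working it through.** **Inputs from the protocol.** 52% versus 70% completion; 80% power and 5% significance; "assuming an intra-cluster correlation coefficient of 0.01"; 4 + 4 clusters; 35 women per cluster.

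**Assumed, because the protocol gives no figure.** D, the difference in completion between hospitals and health centres, taken from 0 to 20 percentage points.

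**The plan's own figures reproduce.** With unpooled variance and a two-sided test, n per arm = (1.960 + 0.842)² × (0.52×0.48 + 0.70×0.30) / 0.18² = 7.85 × 0.4596 / 0.0324 ≈ 111.3, or about 222.7 in total (stated: 222). With 222/8 rounded to 28 per cluster, the design effect is 1 + 27×0.01 = 1.27, and 222 × 1.27 = 281.9 (stated: 282).

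**Variance of a cluster proportion, within type.**
- Between clusters: 0.01 × 0.61×0.39 = 0.002379.
- Within clusters: (0.2496 + 0.2100)/2 / 35 = 0.2298/35 = 0.006566.
- Sum: 0.008945. SE of the arm difference = √(2 × 0.008945/4) = 0.0669.

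**Effect of leaving facility type out.** With one hospital among four clusters in each arm, the type difference adds 2 × (3/4) × D² = 1.5 D² to the residual sum of squares. On 6 df that is 0.25 D² in the mean square. The variance of the arm contrast itself is unchanged. Expected overstatement of the SE:
- D = 5 points: √((0.008945 + 0.000625)/0.008945) = 1.03
- D = 10 points: √((0.008945 + 0.0025)/0.008945) = 1.13
- D = 15 points: √((0.008945 + 0.005625)/0.008945) = 1.28
- D = 20 points: √((0.008945 + 0.0100)/0.008945) = 1.46

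**Price of putting it in.** The df fall from 6 to 5 and the critical t rises from 2.447 to 2.571, a factor of 1.051. The two effects balance when 0.25 D² / 0.008945 ≈ 1.051² − 1 = 0.104, that is D ≈ 6 points.

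**Simulated power and type I error** (linear model on eight cluster means, t reference, 300,000 replicates per scenario; total ICC counts the type difference, which adds variance D² × 3/16):

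| D (points) | Power without type | Power with type | Type I error without type | Total ICC |
|---|---|---|---|---|
| 0 | 61.7% | 58.4% | 5.0% | 0.010 |
| 5 | 58.7% | 58.1% | 4.4% | 0.012 |
| 6 | 57.8% | 58.3% | 4.2% | 0.013 |
| 10 | 51.4% | 58.1% | 3.1% | 0.018 |
| 15 | 40.6% | 58.2% | 1.8% | 0.027 |
| 20 | 28.5% | 58.3% | 0.8% | 0.040 |

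Type I error with facility type in the model stays at 5.0–5.1%. A second simulation of cluster proportions (100,000 replicates) agreed to within about a point: 62% v 59%, 59% v 59%, 52% v 59%, 41% v 59% and 29% v 59% at 0, 5, 10, 15 and 20 points.

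**Holding the total ICC at the planned 0.01.** The type difference must then fit inside 0.002379, so D cannot exceed √(0.002379 × 16/3) ≈ 11 points. Power without and with facility type is 61.5% v 58.1% at D = 0, 60.9% v 60.3% at 5, 59.4% v 68.0% at 10 and 58.9% v 71.0% at about 11. The change therefore runs from about −3 to +12 points.

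**The case against.** **The covariate set is open.** A reader might infer that the plan leaves facility type out of the model. The protocol does not say so: the confounders are unlisted, and an analysis plan that is not shown may include it. Listing covariates is commonly left to that document. This stands, and the supportable statement is that facility type is not named. What remains is that the protocol does give a selection criterion, confounding, and a factor balanced by design does not meet it.

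**The size rests on an undocumented difference.** A reader might also infer that power is lost as a matter of fact. It is not: below a difference of about 5–6 points, adjustment is neutral or slightly harmful. This stands.

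**The large gains do not belong to the planned ICC.** The 15- and 20-point scenarios put the type difference on top of 0.01, giving a total ICC of 0.027 and 0.040; the 10-point scenario already gives 0.018. This stands, and the calculation with total ICC held at 0.01 is the fairer bound under the plan's own assumption.

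**The calculation is not the planned model.** It is a linear cluster-level approximation to a mixed-effects logistic regression, whose degrees of freedom the protocol does not state. With a normal reference there is no df cost: power is about 76% in both models at no difference, and 69% v 76% at 10 points. Type I error at no difference is then about 10–11%. That small-sample problem is separate, and naming facility type does not cure it.

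**No false-positive risk comes from leaving the factor out.** Correct. Omission lowers the type I error, and stratification still balances the arms.

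**Conclusion.** The point holds in a conditional form. The design stratifies on facility type, the models do not name it, and the stated covariate criterion would not bring it in. If completion differs between primary hospitals and health centres, the standard error is too large for the design used and the t-based test is conservative.

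With an ICC of 0.01 within type and 35 women per cluster, naming the factor costs about 3 points of power at worst and gains about 7 at a 10-point difference. With the total ICC kept at 0.01, the range is −3 to +12 points. The gains of 18–30 points require differences of 15–20 points and more clustering than was planned.

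These figures rest on the inferred one-and-three split per arm, the cluster-level approximation with small-sample t, and an assumed range for the difference. The documents do not support a claim that facility type is excluded, that power is certainly lost, or that the arm comparison is biased. The possible loss from adjusting is small and bounded, so the factor is worth naming in advance.

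**What to change.** State in the protocol or analysis plan that facility type (primary hospital / health centre) enters the primary model and each secondary outcome model as a fixed effect, alongside the facility random intercept. It is to be kept whatever its significance and whatever the baseline comparison shows. List it as the stratification factor, separately from the potential confounders.

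The cost is one sentence and one between-cluster degree of freedom (6 to 5 for the arm effect), or about 3 points of power if the two facility types turn out alike. No new data are needed and recruitment is unaffected. The sentence should be fixed before outcome data by arm are examined.

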### Concealment mechanism {16b}

A lottery method was used to cluster-randomise health facilities into either the control group or the intervention arm, ensuring an unbiased distribution of facilities across the two groups.

### Implementation {16c}

The DINKNESH referral and follow-up app is hosted on a secure server at Addis Ababa University. Sixteen health professionals, two per facility, have been trained and will be responsible for using the app to manage referrals based on eligibility criteria and their clinical decisions. Tablets with the DINKNESH referral and follow-up app installed will be provided to the trained health professionals at each facility. At the primary healthcare facilities, the tablets will be given to professionals working in the outpatient department. At the referral hospitals, nurses working in the surgical outpatient department will be responsible for using the app to receive referrals.

## Assignment of interventions: blinding

### Who will be blinded {17a}

Not applicable: Because this is a cluster randomised controlled trial with the intervention implemented at the health system level, blinding is not feasible.

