### Outcomes {12}

Primary outcome: Proportion of successfully completed referrals.

Definition of primary outcome: A successfully completed referral is defined as a case in which, after study inclusion, a patient initiates the first diagnostic or treatment procedure at the receiving external institution and feedback is received by the referring institution within 60 days of the referral.

Secondary outcomes:Time from initial presentation at the health facility to first diagnosis for women with breast-related abnormalitiesProportion of internal referrals within the facilityProportion of breast cancers detected at an early stage

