### Procedure for unblinding if needed {17b}

Not applicable: Blinding will not be implemented in this study.

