## Data collection and management

### Plans for assessment and collection of outcomes {18a}

#### Primary outcome (proportion of complete referrals)

For the intervention group, the referral status will be digitally recorded. Time intervals from the woman’s initial visit to the facility to when the referral is sent and when feedback is received will be used to calculate the proportion of complete referrals. In the control group, referrals will be managed through routine paper-based procedures. Sixty days after the referral, trained data collectors will review medical records at both the sending and receiving facilities to determine whether feedback was received. The use of a standardised data extraction tool, aligned with the variables used in the DINKNESH referral and follow-up app, will ensure comparability between the two groups.

To further explain the outcome variable, baseline data will be collected from both groups after consent, including sociodemographic information, clinical data, and knowledge of breast cancer. The African Women Awareness of CANcer (AWACAN) tool will be used to assess awareness, health-seeking behaviour, and perceptions. This baseline information will help interpret the primary outcome [23].

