## Discussion

The WHO recommends integrating digital health services to strengthen health systems and advance universal health coverage [27]. In addition, the WHO’s GBCI emphasises early detection and timely referral of suspected breast lesions to ensure early diagnosis [5]. However, evidence on the impact of digital health in primary cancer care—particularly in low-resource settings—remains limited [28]. This study aims to help fill that gap by evaluating a digital referral system designed to support early breast cancer detection and contribute to the GBCI goal of diagnosing 60% of women at an early stage.

The lack of blinding is a limitation of this study because it may introduce bias. Additionally, the relatively short follow-up period of 60 days may restrict understanding of the longer-term referral process following diagnosis. Because the study follow-up focuses primarily on the time to early diagnosis, subsequent referrals for treatment and ongoing care may not be captured.

A key strength of this study is its focus on peripheral health settings, where evidence remains scarce. It also contributes to capacity building by providing CBE training to healthcare providers. Furthermore, the embedded qualitative study will explore the implementation challenges and user experiences associated with the DINKNESH referral and follow-up app, offering valuable insights to inform future scale-up plans. The intervention is expected to increase the proportion of completed referrals and improve the early diagnosis of breast abnormalities by addressing referral delays caused by poor communication between facilities. Moreover, it will provide policymakers with insights into the use of digital referral systems in cancer care, including both challenges and opportunities for broader implementation.

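### The protocol rules out all blinding because the intervention is at system level, but that reason does not reach central outcome derivation or the statistician, who can be masked cheaply

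*Protocol article*

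**What the plan says.** Under Who will be blinded {17a} the protocol article answers that the item is not applicable and explains: "Because this is a cluster randomised controlled trial with the intervention implemented at the health system level, blinding is not feasible". The item that follows, {17b} on unblinding, adds: "Blinding will not be implemented in this study". Neither item separates participants, care providers, outcome assessors and analysts. The Discussion returns to the subject once: "The lack of blinding is a limitation of this study because it may introduce bias". It names no measure to limit that bias.

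Three other places bear on what could be masked:

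- **Outcomes {12}** counts a referral as completed when "a patient initiates the first diagnostic or treatment procedure at the receiving external institution and feedback is received by the referring institution within 60 days".
- **Plans for assessment and collection of outcomes {18a}** gives each arm its own source. In the intervention arm: "For the intervention group, the referral status will be digitally recorded". In the control arm, sixty days after referral, "trained data collectors will review medical records at both the sending and receiving facilities to determine whether feedback was received". Comparability is to come from "The use of a standardised data extraction tool, aligned with the variables used in the DINKNESH referral and follow-up app".
- **Statistical methods {20a}** plans a mixed-effects logistic regression "adjusting for potential confounders and accounting for clustering at the health facility level".

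**The concern.** In an open cluster trial, blinding is a separate question for each role. A system-level intervention explains why some roles must know the arm. It is not a reason for every role to know it. The two blinding items treat the question as settled for everyone, so as written the trial gives up protection at the two steps where it is easiest to have: turning recorded events into the binary endpoint, and fitting the primary model.

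The endpoint has parts that may need interpretation, namely what counts as a first diagnostic or treatment procedure and what counts as feedback. The early-stage secondary outcome may need it too. If a person who knows the arm settles doubtful entries, they may drift towards the expected result. The same holds for modelling decisions taken with arm labels in view. With 8 facilities and about 35 women in each, it does not take many women to move an arm's proportion by several points.

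**Working it through.** **1. Does the stated reason cover each role?**

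- *Women and facility staff.* Staff in the intervention arm use the app and women there receive its reminders. The reason holds.
- *Field data collectors.* Control outcomes come from reading records at the sending and receiving facilities; intervention outcomes come from the app. The source itself reveals the arm, so masking is not realistic.
- *Whoever derives the endpoint centrally.* This step needs dates, procedure and feedback entries, not the arm. The aligned extraction tool means that both sources can supply the same variables, so they can be merged with facility and arm replaced by neutral codes. The reason does not hold.
- *The statistician.* The model needs a cluster identifier and an arm indicator, and both can be codes. According to the data collection and data management sections, baseline data are gathered in both arms and entered in one electronic system, so they need not show the source. The reason does not hold.

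**2. The plan's own sample size, as a base for scale.** Inputs from Sample size {14}: 52% versus 70%, 80% power, 5% significance, intra-cluster correlation 0.01, 8 clusters in a 4:4 split. With unpooled variance and a two-sided test:

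- n per arm = (1.96 + 0.84)² × (0.52×0.48 + 0.70×0.30) / 0.18² = 111.3 with unrounded normal quantiles, so 222.7 in total. The plan states 222.
- Design effect at 222/8 = 27.75 per cluster: 1 + 26.75×0.01 = 1.2675. Then 222 × 1.2675 = 281.4, rounded up to 282. The plan states 282.

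Both figures reproduce. Masking changes neither.

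**3. What a few reclassified women would do (assumption, not a figure in the documents).** Recruitment {15} fixes 35 per facility, so 4 × 35 = 140 per arm.

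- 5 women in one arm: 5/140 = 3.6 points.
- 5 in each arm, all errors favouring the same conclusion: 10/140 = 7.1 points.
- Standard error of the difference at the planned rates, with design effect 1 + 34×0.01 = 1.34: √[(0.2496 + 0.2100) × 1.34 / 140] = 0.066, or 6.6 points.
- The two shifts are therefore about 0.5 and 1.1 standard errors.

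**4. The same idea as a false-positive rate (also assumption).** Suppose there is no true effect: 52% in both arms, 140 per arm, design effect 1.34, normal test. A fraction f of intervention-arm non-completions is recoded as completed, which shifts that arm by 0.48f.

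| f | Shift (points) | Two-sided rejection probability |
|---|---|---|
| 0 | 0 | 5.0% |
| 2% | 1.0 | 5.2% |
| 5% | 2.4 | 6.4% |
| 10% | 4.8 | 10.7% |

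About 67 women per arm would be non-completers (0.48 × 140), so 5% is 3 to 4 women and 10% is 6 to 7. Small misclassification does little; the effect becomes material only towards the bottom row.

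**The case against.** **The judgement may already have been made in the field.** Data collectors who know the arm decide whether feedback was received, and a masked central coder would inherit their entries. This stands. Central masking cannot undo it, and the difference in ascertainment between arms is a separate problem that this change leaves in place.

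**The endpoint is defined by events and a time limit, so there may be little to judge.** This stands in part. A fixed rule does most of the work at the derivation step, and the documents do not report how many entries would be doubtful. Masking then mainly protects the cases that the rule does not settle, and the analysis. For stage, no section says that a trial coder assigns it, so masking applies only if it is derived centrally.

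**The limitation is disclosed.** It is, but disclosure does not correct the statement that blinding is infeasible for everyone.

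**A stronger reading is tempting:** that people who know the arms will choose the confounders and the missing-data method during analysis. The documents do not establish this. The article names no covariates, and its missing-data section makes the approach depend on the type of missingness and adds a sensitivity analysis. Covariate lists and missing-data rules commonly sit in a statistical analysis plan, which is not shown here and may fix both beforehand. A reader might also infer that the Discussion accepts the bias as unavoidable; it says only that bias may arise.

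**Conclusion.** The point holds in a limited form. The reason given for having no blinding applies to participants, facility staff and field data collectors. It does not apply to central outcome derivation or to the statistician, yet the two blinding items exempt no role. This rests on those items alone and not on the absence of a covariate list.

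The size of any resulting bias cannot be derived from the documents. The 3.6-point figure assumes 5 reclassified women in one arm, and the 7.1-point figure further assumes that every error in both arms pushes the same way. Neither shows that the trial's conclusion would change. The change is worth making because it replaces a blanket statement with a safer procedure at little cost. It is an inexpensive improvement, not a flaw that invalidates the design.

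**What to change.** Reword the two blinding items to state that:

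1. Participants, facility staff and field data collectors are unblinded.
2. App data and control extraction data are merged into one file in which facility and arm appear only as neutral codes.
3. Completed or not completed is derived from that file by a fixed written rule applying the protocol's existing definition. Early or late stage is handled the same way where it is derived centrally.
4. The primary model is finalised and run on coded arms before the code is opened.
5. The key is held by an existing team member who is not the analysing statistician. This must be explicit: the supervisory team described under {5d} includes a statistician, so giving the key to the team as a whole could unmask the analyst.

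The Discussion sentence should then say which roles were unblinded and that the arms' outcomes were ascertained differently.

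The cost is one extra data-management step and an amendment notified through the route in {25}. No visits are added and the sample size is unchanged. Enrolment began on 30 November 2024, but these steps follow data collection, so the change remains possible if derivation and analysis have not started. Masking will be imperfect where record patterns give away the source.
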